### Quantitative statistical analysis plan

The data will be stored in PCN clinical database and will be extracted after the 12-month intervention and passive period. We will assess the outcome at baseline, 3-month, 6-month, and 12-month time points. The data will be analyzed for multiple time points to allow for a comparison between immediate and long-term provider impact and to increase the reliability of observed trends. Following the sustainability period of 12 to 24 months, the data will be extracted again, and analyzed by blinded data analysts.

### Primary outcomes

Two stage summary statistics will be used for the analysis of the primary outcome; the number of weight management visits/FTE for each practitioner will be derived for each time point, and the average of the weight management visits/FTE for the intervention and the control group will be calculated. Weight management visit/FTE trends at pre-intervention, baseline, 3, 6, 12 and 18 months post intervention will be plotted to compare the two groups.

The intervention group and control group will be compared using Wilcoxon-Mann–Whitney test. As generalized estimating equation (GEE) can adjust for clustering effect and does not require a normal distribution, we will perform GEE models to compare the 5AsT intervention group and the control group for our primary outcome at 3, 6, 12 and 18 months. Analysis will be by intention to treat.

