### Allocation concealment and randomization

Following ethical approval and study registration, the eligible clinics (N = 24) were allocation concealed and randomized in a 1:1 ratio using a computer generated random sequence by a statistician external to the project. Randomization was stratified for larger vs. smaller patient panel sizes. Three strata with eight practices were created from the 24 eligible practice units. The first 8 units (Group 1) have panel size ≤2,754; Group 2 has clinic panel size from 2,755 to 6,576, and Group 3 has clinic panel size ≥6,577.

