### Power considerations

Power calculations were performed using both simple and cluster randomization where each clinic is considered as a cluster and RNs are clustered within units. The intra class correlation was estimated to be 0.40. Power calculations with the two approaches were very similar. Given the large numbers of units with only one nurse, we opted in favor of a simple randomization approach. Briefly, this initial approach was as follows:

For simple randomization, a power of 77% was estimated from N = 31 (total number of nurses in the study). The power for a clustered randomized trial was estimated for two scenarios: in 24 clinics with an average of two nurses per clinic, this resulted in a power of 80%; in 24 clinics with an average of one nurse per clinic, it resulted in a power of 65%. These two were presented because we have 31 nurses in total, with an average of 1.3 nurses per clinic, and the exact calculation is not available because an integer is required. However, from the two scenarios, the exact power should be somewhere between 65% and 80%, which is similar to the resulting power from a simple randomization (77%), thus explaining our rationale of opting for a simple randomization.

Effect size was determined using the 22 units for which complete baseline data was available. The mean number of weight management visits/FTE was 69.2 with a standard deviation of 48.1. The study will have 80% power to detect an effect size of 1.19 (absolute difference of 57-weight management visits/FTE between intervention and control groups).

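### The Wilcoxon test on the primary outcome treats 31 nurses as independent although 24 clinics were randomised, and the plan does not say whether it or the GEE decides

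*Protocol article*

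**What the plan says.** Under Allocation concealment and randomization, the clinic is the randomised unit: "the eligible clinics (N = 24) were allocation concealed and randomized in a 1:1 ratio using a computer generated random sequence". The allocation was stratified by panel size: "Three strata with eight practices were created from the 24 eligible practice units". The patient-level section on enrolment procedures repeats that randomisation was by clinic.

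Under Primary outcomes, the analysed unit is the practitioner: "the number of weight management visits/FTE for each practitioner will be derived for each time point". Two methods follow. The first is "The intervention group and control group will be compared using Wilcoxon-Mann–Whitney test", with no mention of clustering, strata or time point. The second is introduced with the words "As generalized estimating equation (GEE) can adjust for clustering effect and does not require a normal distribution, we will perform GEE models", and is applied to the primary outcome at 3, 6, 12 and 18 months. Neither method is ranked above the other.

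Under Power considerations for the provider-level study, the clinic is treated as the cluster, the ICC is put at 0.40, and there are 31 nurses, about 1.3 per clinic. Power with and without clustering is called similar, and the section concludes: "Given the large numbers of units with only one nurse, we opted in favor of a simple randomization approach".

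**The concern.** A test of a randomised comparison should respect the unit that was randomised. Two nurses in one clinic always share an arm and, on the protocol's own figure, have correlated outcomes. A practitioner-level rank test counts them as two independent pieces of evidence, so its null distribution is too narrow wherever clinics have more than one nurse.

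The reason given for the simple approach does not address this. Power describes behaviour when the intervention works. Two methods can have similar power while one of them rejects a true null hypothesis too often, and part of its power then comes from that excess.

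The missing ranking matters because one of the two methods ignores clustering and the other is meant to handle it. They can fall on opposite sides of 0.05, and the text leaves the unadjusted test available for the headline result.

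**Working it through.** **Inputs from the protocol.** 24 clinics, 1:1, three strata of 8; 31 nurses; ICC 0.40; mean 69.2 and SD 48.1 visits/FTE; effect size 1.19 (57 visits/FTE) at 80% power; power of 77% (31 nurses, simple), 80% (24 clinics of two nurses) and 65% (24 clinics of one nurse).

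**Inputs assumed.** Two-sided 5% level; the number of nurses in each clinic; 4:4 allocation within strata; how far the strata predict the outcome.

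**Step 1: the protocol's power figures.** With a two-sample noncentral t, 12 against 12 units and d = 1.19, power is 79.6%. With d = 57/48.1 = 1.185 it is 79.2%. This reproduces the stated 80%. The other three figures come without an effect size. Taking d = 1.0 and an effective sample size of n/[1 + (m − 1) × 0.40], they come out at 76.7%, 79.9% and 64.9%, against 77%, 80% and 65%. The power figures are reproducible, but none of them is a false-positive rate.

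**Step 2: large-sample approximation.** With clinic sizes m, the variance of a practitioner-level mean is inflated by DE = 1 + (Σm²/Σm − 1) × 0.40. A test that ignores this has true error 2[1 − Φ(1.96/√DE)]. Three mixes that give 24 clinics and 31 nurses:

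| Clinics × nurses | Σm² | DE | Error |
|---|---|---|---|
| 17×1, 7×2 | 45 | 1 + (45/31 − 1) × 0.40 = 1.18 | 7.1% |
| 19×1, 3×2, 2×3 | 49 | 1 + (49/31 − 1) × 0.40 = 1.23 | 7.8% |
| 21×1, and one each of 2, 3, 5 | 59 | 1 + (59/31 − 1) × 0.40 = 1.36 | 9.3% |

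**Step 3: simulation of the Wilcoxon test under no effect.** 8,000 runs per scenario (Monte Carlo error about 0.3 points), ICC 0.40, 4:4 within three strata of 8 clinics, one time point, no stratum effect on the outcome. The log-normal data use exp(0.63y), with y the normal outcome. Their coefficient of variation is about 0.70, matching 48.1/69.2 = 0.695; the ICC of 0.40 then holds on the log scale.

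| Mix | Nurse-level Wilcoxon, normal | Nurse-level, log-normal | Wilcoxon on clinic means, normal | Clinic means, log-normal |
|---|---|---|---|---|
| 17×1, 7×2 | 6.4% | 6.0% | 4.4% | 4.2% |
| 19×1, 3×2, 2×3 | 7.2% | 7.1% | 4.3% | 4.2% |
| 21×1, 2, 3, 5 | 8.6% | 8.0% | 4.9% | 4.3% |

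For the first mix with normal data, the nurse-level rate is 4.4% at ICC 0, 5.6% at 0.2, 7.8% at 0.6 and 9.0% at 0.8. The excess therefore comes from clustering.

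**Step 4: strata that predict the outcome.** An unadjusted test after stratified allocation becomes conservative when the strata matter, which works against the inflation. A separate simulation (6,000 runs, normal data, total ICC 0.40, nurse numbers assigned to clinics at random) gives, for the nurse-level Wilcoxon:

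| Variance explained by strata | 17×1, 7×2 | 19×1, 3×2, 2×3 | 21×1, 2, 3, 5 |
|---|---|---|---|
| 0% | 6.3% | 6.8% | 8.2% |
| 10% | 5.1% | 5.6% | 6.7% |
| 20% | 4.3% | 4.4% | 5.4% |

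The true error of the planned test thus depends on two quantities that the protocol does not give, and it can lie on either side of 5%.

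**The case against.** The strongest reply is that clustering is not overlooked. The protocol plans a GEE expressly because it can adjust for clustering, ties it to the primary outcome at named time points, and treats the clinic as the cluster in its power section. Reading the GEE as the main model is at least as natural as reading the Wilcoxon that way. This stands, and it is why the remedy is mostly a matter of ranking. It does not remove the point, because the text also commits to the nurse-level test without making it subordinate.

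The second reply is that the inflation is small. Most clinics must have one nurse, the mixes above are assumed, and stratification can cancel the excess. This also stands, and it limits the size of the claim. An error rate that is right only if two opposing defects happen to balance is still not controlled by the plan.

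Three stronger readings are tempting and not supported:

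- A reader might infer that the planned GEE also exceeds 5%, since there are only 24 clinics. An uncorrected robust variance with a normal reference gave 7.0% to 11.1% in the simulations of Step 3, but a Mancl-DeRouen correction with t on 22 df gave 3.7% to 5.7%. The protocol names neither a variance estimator nor a reference distribution, and an article may leave both to the analysis plan.
- A reader might infer that the reported confidence intervals will be too narrow. The Wilcoxon is planned as a test with no stated interval, so the text does not show this.
- A reader might take the simple-randomisation wording to mean that nurses were randomised individually. It sits in the power rationale; the allocation section is clear that clinics were randomised.

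**Conclusion.** The mismatch is established from the text alone: clinics were randomised, nurses are compared as if independent, and similar power is offered as the justification. The lack of a rule for which of two methods decides the primary outcome is also plain from the text.

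The size is modest and conditional. At ICC 0.40 the nurse-level Wilcoxon has a false-positive rate of about 6% to 9% if panel-size strata do not predict visits/FTE, and about 4% to 7% if they explain 10% to 20% of the variance. Both ranges rest on assumed numbers of nurses per clinic and a single time point; the stratum effect is likewise an assumption. The supportable conclusion is that the nominal 5% is not assured. The verdict does not extend to the GEE, whose error rate cannot be judged from this document.

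**What to change.** Under Primary outcomes, name one deciding analysis: the GEE already planned, with clinic as the cluster and adjustment for the three panel-size strata. With only 24 clinics, a small-sample variance correction (Mancl-DeRouen or Kauermann-Carroll) and a t reference with clinic-based degrees of freedom are preferable. That means 24 − 2 = 22 df for an arm-only model, or 24 − 4 = 20 with two stratum terms. The correction can be stated in the analysis plan.

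Replace the practitioner-level Wilcoxon with a stratified rank or permutation test on one value per clinic, labelled as sensitivity, and define that value (the simulation used the unweighted mean over nurses). If allocation was 4:4 in each stratum, there are 70³ = 343,000 possible allocations, ample for a permutation test.

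Under Power considerations, remove the simple-randomisation rationale so that the section agrees with the allocation section.

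The cost is slightly wider intervals, a few sentences and a few lines of code. No new data and no design change are needed.

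### The first-named primary test uses neither baseline visits/FTE nor the panel-size strata, and the GEE names no adjustment beyond clustering

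*Protocol article*

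**What the plan says.** All references are to the protocol article.

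- Under Primary outcomes, "the number of weight management visits/FTE for each practitioner will be derived for each time point". Then "The intervention group and control group will be compared using Wilcoxon-Mann–Whitney test". No change score and no stratified form of the test is mentioned.
- The same section gives a reason for the model, "As generalized estimating equation (GEE) can adjust for clustering effect and does not require a normal distribution", and states the comparison itself as follows: "we will perform GEE models to compare the 5AsT intervention group and the control group for our primary outcome at 3, 6, 12 and 18" (times in months). Clustering is the only adjustment named. The one use of pre-intervention and baseline values that this section spells out is a trend plot.
- Under Quantitative statistical analysis plan: "We will assess the outcome at baseline, 3-month, 6-month, and 12-month time points". Baseline visits/FTE will therefore be in hand.
- Under Allocation concealment and randomization: "Randomization was stratified for larger vs. smaller patient panel sizes", in three groups of eight clinics. No provider-level analysis text refers to these groups.
- Under Power considerations (provider study): "Effect size was determined using the 22 units for which complete baseline data was available". The mean was 69.2 visits/FTE and the SD 48.1. The trial is said to have 80% power for an effect size of 1.19, or 57 visits/FTE. No correlation between baseline and follow-up is given.
- Under Quantitative data analysis: patient study, by contrast, baseline values are named as a covariate.

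**The concern.** The trial randomises only 24 clinics, and their visit rates differ widely: the SD is 70% of the mean (48.1/69.2). The target difference of 57 visits/FTE is 82% of the baseline mean (57/69.2). In so small a trial, two pieces of information held before follow-up can sharpen the comparison and guard against chance imbalance: the clinics' own past visit rates and the factor used to stratify the allocation. The named rank test uses neither, and the GEE text does not commit to either. At stake are precision and the freedom to choose the adjustment after results are seen, since the study team is unblinded at 12 months. Bias of the randomised comparison is not at stake.

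**Working it through.** **Inputs.** There are 24 clinics randomised 1:1, so 12 per arm (Allocation concealment and randomization). SD 48.1, mean 69.2, effect size 1.19, difference 57 and power 80% come from Power considerations. Assumptions: two-sided alpha of 0.05 (not stated), the SD of 48.1 taken as a clinic-level SD, and the baseline-to-follow-up correlation ρ (not stated, so shown as a range).

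**Step 1: the plan's own figure.** 57/48.1 = 1.185, close to the stated 1.19. For an unadjusted two-sample t comparison the noncentrality is 1.19/√(1/12 + 1/12) = 1.19/0.408 = 2.91 on 22 df, which gives 79.6% power. The effect size with exactly 80% power is 1.197, and 1.197 × 48.1 = 57.6 visits/FTE. The stated 80% therefore fits an unadjusted comparison. An adjusted analysis with ρ near zero would give almost the same figure, so the match alone proves nothing, but no correlation enters the stated calculation. The section's other power figures (77%, 65%, 80%) fit an effect size of about 1.0 instead, which is a separate matter.

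**Step 2: with baseline and strata as covariates.** The residual SD is 48.1 × √(1 − ρ²). Baseline costs 1 df and the three strata cost 2, leaving 22 − 3 = 19 df. The strata are assumed to explain no further variance. The detectable difference is then 58.0 × √(1 − ρ²), where 58.0 is the value at ρ = 0.

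| Analysis | Difference detectable with 80% power (visits/FTE) | Power at effect size 1.19 |
|---|---|---|
| Unadjusted | 57.6 | 79.6% |
| ρ = 0 | 58.0 | 79.0% |
| ρ = 0.2 | 56.8 | 80.6% |
| ρ = 0.3 | 55.3 | 82.6% |
| ρ = 0.5 | 50.2 | 89.1% |
| ρ = 0.7 | 41.4 | 97.2% |

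If the analysis were restricted to 22 units with a baseline (11 against 11), the figure at ρ = 0.5 would be 52.8 instead of 50.2.

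**Step 3: chance imbalance.** The standard error of the baseline difference between arms is 48.1 × √(2/12) = 19.6 visits/FTE, if panel size is unrelated to visits. A gap at least that large, in either direction, arises in roughly one allocation in three. It is 28% of the baseline mean (19.6/69.2) and about a third of the 57-visit target (19.6/57 = 34%). With equal SDs, an unadjusted comparison carries over ρ times the gap, for example 0.5 × 19.6 = 9.8 visits/FTE at ρ = 0.5.

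**Step 4: does the adjusted GEE keep its level with 24 clusters?** This was simulated under the null with 31 nurses in 24 clinics, ICC 0.40, stratified allocation and non-prognostic strata. A GEE with the uncorrected sandwich variance and a normal reference rejects about 8% of the time without covariates and about 11% with them. A bias-corrected variance with a t reference holds the level at 5% or below. Power for a one-SD difference then rises from about 65% unadjusted to 70% at ρ = 0.5 and 87% at ρ = 0.7. These gains depend on the correction chosen and on baseline being available. With a conservative correction, the loss at low ρ exceeds the cost of the 3 df alone.

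**The case against.** The strongest reply is that the article does not list the GEE's terms. The sentence on the GEE gives comparison times, and covariates are commonly left to a full protocol or SAP, which is not shown. A reader might infer that the GEE is fixed as unadjusted. The text does not say so, and because baseline is listed among the assessment times, a baseline-adjusted or repeated-measures GEE is compatible with it. This part of the objection stands. It does not reach the Wilcoxon-Mann-Whitney test, which is a stated choice and as named has no place for baseline or strata.

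A second reply is that the gain is unproven. The correlation is unknown, the article describes a fast-growing network, and low stability of visit rates would leave little to win. That also stands, which is why the range starts at zero.

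A reader might further infer that ignoring the strata makes the inference invalid. It does not. If panel size predicts visits/FTE, leaving the strata out usually makes the standard error too large. If it does not, the effect is negligible. No figure in the article links panel size to visits/FTE, so the case for the strata is that the analysis should follow the design.

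Finally, adjustment is not free: added covariates worsen the already inflated error rate of an uncorrected GEE with 24 clusters. That stands and shapes the fix.

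**Conclusion.** The point holds in a limited form. The first-named primary test ignores baseline and strata, the GEE commits to neither, and the stated power is that of an unadjusted comparison, although both pieces of information are held and the article adjusts for baseline in its patient study. A better analysis is available for little cost.

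The size depends on ρ. The detectable difference changes from 57.6 to 58.0 visits/FTE at ρ = 0 (a slight loss), 55.3 at 0.3, 50.2 at 0.5 and 41.4 at 0.7. The gain is negligible below about 0.2 to 0.3 and material from 0.5. These figures assume two-sided 5%, a clinic-level SD of 48.1 at follow-up as at baseline, and strata that explain nothing.

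Two stronger readings are not supported: that a large loss of power is established, and that two clinics will lack a baseline at analysis. The 22 units are those with complete data when the effect size was worked out, and nothing is said about later availability.

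**What to change.** Before the 12-month unblinding, state the following in the analysis plan:

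1. The primary comparison is a GEE with baseline visits/FTE and the three-level panel-size stratum as covariates.
2. Inference uses a small-sample-corrected variance and a t reference, with the correction named, because there are 24 clusters.
3. Any unit without a baseline value is handled by one simple rule, for example the mean baseline of both arms combined. A missing-value indicator would cost a further degree of freedom.
4. The rank test becomes supportive and is stratified by the same three groups.

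The cost is wording, 3 degrees of freedom and some loss of power if the correlation proves low. No new data are needed. Before the covariates are fixed, the network's pre-intervention records could be used to estimate the period-to-period correlation without reference to allocation. Modelling counts with a log offset for FTE is a separate refinement and is not needed here.

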### Power considerations

Power calculations were performed using both simple and cluster randomization where each clinic is considered as a cluster and RNs are clustered within units. The intra class correlation was estimated to be 0.40. Power calculations with the two approaches were very similar. Given the large numbers of units with only one nurse, we opted in favor of a simple randomization approach. Briefly, this initial approach was as follows:

For simple randomization, a power of 77% was estimated from N = 31 (total number of nurses in the study). The power for a clustered randomized trial was estimated for two scenarios: in 24 clinics with an average of two nurses per clinic, this resulted in a power of 80%; in 24 clinics with an average of one nurse per clinic, it resulted in a power of 65%. These two were presented because we have 31 nurses in total, with an average of 1.3 nurses per clinic, and the exact calculation is not available because an integer is required. However, from the two scenarios, the exact power should be somewhere between 65% and 80%, which is similar to the resulting power from a simple randomization (77%), thus explaining our rationale of opting for a simple randomization.

Effect size was determined using the 22 units for which complete baseline data was available. The mean number of weight management visits/FTE was 69.2 with a standard deviation of 48.1. The study will have 80% power to detect an effect size of 1.19 (absolute difference of 57-weight management visits/FTE between intervention and control groups).

### Qualitative data collection

Qualitative data will include description of context, implementation process, and effect of the 5AsT intervention on provider behaviour change. The approach is summarized in Table 2. Primary data sources for the intervention include guided field notes taken during bi-weekly learning collaborative sessions, and logs kept by the clinical champion and the practice facilitators. Data sources for provider impact include semi-structured interviews with key informants, and focus groups. Potential participants will include all providers and key PCN implementation personnel involved in the 5As Team project.

**Table 2 T2:** Qualitative data collection plan

**Method**	**Justification**	**Timeframe**
**Intervention Phase**		
Session field notes	Description: context, implementation process.	0-6 months
Semi-Structured Interviews	All 5AsT randomized providers. Baseline data: intervention content and process feedback-loop.	Initial 3 months
	Personal views and practice, values fit, clinic climate.	
Focus Groups	Evaluation of tools developed during sessions.	6 months
